### 2.5 Blinding

This study would be an open label trial. Due to the different nature of the visible marks of the sutures, it would not be possible to blind the study team, the PI, the surgeon, and the outcome assessor (SSI nurse) from the intervention administered. The surgical site infection nurse who assesses the surgical wounds post-operatively in the hospital as well as in clinics during follow up visits would be blinded to the hypothesis of the study. The other outcome assessors such as the pathologist who will conduct tests on the specimen taken from the surgical site, to confirm the presence of an infection would be blinded to the intervention.

### 2.6 Study Population

All bilateral simultaneous knee arthroplasty patients presenting at the outpatient clinics and opting to undergo surgery at AKUH Karachi, Pakistan.

### 2.7 Eligibility Criteria

#### 2.7.1 Inclusion Criteria

The study will include the adult patients of age 40–70 years [6], undergoing bilateral simultaneous knee arthroplasty at AKUH Karachi. Patients from both the genders would be included. Patients having American Society of Anesthesiologists (ASA) level of I, II and III pre-operatively would be included in the study. Patients having functional class of I, II and III pre-operatively would be included in the study. Only Patients opting for elective bilateral simultaneous knee arthroplasty would be included in the study, as emergency conditions such as trauma or fracture may complicate wound closure(3]. Only those patients would be included in the study who are opting to undergo bilateral simultaneous knee arthroplasty under care of the selected surgeon (A) for the study. Patients undergoing surgery should have the midline incision and through para-patellar approach used for making the incision will be included in the study.

#### 2.7.2 Exclusion Criteria

The Patients who are unwilling to consent and the patients unable to comprehend due to the language barrier will be excluded. Patients who have a Glasgow Coma Scale i.e. GCS<15 (cognitive impairment) will be excluded. Patients undergoing a knee revision surgery would be excluded from the study [16]. Patients having a previous incision/scar in the operative field will be excluded [1]. Patients having documented allergy to Prolene or stainless steel would be excluded [8]. Patients having a documented underlying malignancy will be excluded [3]. Patients undergoing unilateral TKR or staged bilateral simultaneous TKR would also be excluded from the study.

### 2.8 Sample Size

The sample size was calculated via open epi software version 3.01. The level of significance was kept at 5% with a power of 80%. The percentage of exposed (staple sutures) with outcome (surgical site infection) was 66%. The percentage of non-exposed (Prolene sutures) with outcome (surgical site infection) was 33%. The estimated risk ratio taken from a study was 2. After adding the non-response rate of 10% the final sample size came out to be 82 patients with 41 patients in each arm [3].

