### 2.4 Randomization

The patients would be randomized in 1:1 allocation to either receive Prolene sutures or the staple suture. Randomization will be done by the clinical trials unit (CTU) of AKUH using the specialized computer software. The computer-generated random allocation will ensure that nobody including the investigator, or the study team are able to influence it. Simple randomization process will be carried out using a block technique to assign the allocation. After completing the process of randomization, the details identifying the patient and the envelope number would be recorded on a form and will be returned to the trial administration to confirm the recruitment of the patient into the study.

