### 2.10 Outcomes

#### 2.10.1 Primary Outcome

Primary outcome of the study is the incidence of surgical site infection (superficial or deep) within 6 weeks for superficial infections and 90 days for deep infections. SSI is defined as an infection that occurs after surgery in the part of the body where the surgery took place within 90 days of surgery [13]. Based on the literature, we anticipate infection rate in the range of 2%–7% [14,15].

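### The sample size rests on infection rates of 66% and 33%, but the protocol anticipates 2%–7%; at those rates 82 patients fall far short of 80% power and about 2–6 infections are expected

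*Protocol article*

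**What the plan says.** Section 2.8 (Sample Size) gives these inputs:

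- Error rates: "The level of significance was kept at 5% with a power of 80"%.
- Staples: "The percentage of exposed (staple sutures) with outcome (surgical site infection) was 66"%.
- Prolene: "The percentage of non-exposed (Prolene sutures) with outcome (surgical site infection) was 33"%.
- Effect: "The estimated risk ratio taken from a study was 2".
- Result: "After adding the non-response rate of 10% the final sample size came out to be 82 patients with 41 patients in each arm".

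Section 2.10.1 (Primary Outcome) defines the primary outcome as superficial SSI within 6 weeks or deep SSI within 90 days. It then states, on the basis of the literature, that "we anticipate infection rate in the range of 2%–7"%.

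Section 5 intends the results to go to all surgeons of the service line so that practice becomes standard.

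**The concern.** Both sections describe SSI in the same trial population, yet the planning rates are about 5 times (33/7) to 33 times (66/2) the anticipated ones. Nothing in the article explains the gap.

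Power for a binary outcome depends on the absolute rates as well as on the risk ratio. A doubling from 33% to 66% is a 33-point difference and needs few patients. A doubling from 2% to 4%, or from 3.5% to 7%, needs many hundreds per arm. If Section 2.10.1 is right, a true doubling of infections would almost always be missed. The non-significant result would then come from a trial described as having 80% power, and could be passed to surgeons as grounds for treating the two closures alike.

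**Working it through.** **Inputs.** From Section 2.8: 66% and 33%, risk ratio 2, alpha 5% (taken as two-sided; the article does not say), power 80%, 10% non-response, 82 patients. From Section 2.4: 1:1 allocation by patient. From Section 2.10.1: 2%–7%.

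**Step 1: reproduce the plan's figure.** The Kelsey formula for two proportions is

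n per arm = (z₀.₉₇₅ + z₀.₈₀)² × 2 × p̄(1 − p̄) / d²

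with p̄ = (0.66 + 0.33)/2 = 0.495 and d = 0.33:

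n = 7.849 × 2 × 0.495 × 0.505 / 0.1089 = 36.03, rounded up to 37.

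Adding 10%: 37 × 1.10 = 40.7, rounded up to 41 per arm, or 82 in total. This matches the plan. Other variants fit less well:

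- Fleiss without continuity correction gives 35 per arm, and 78 in total after the 10%.
- Fleiss with continuity correction gives 41 per arm before the 10% is added, and 92 in total after it.

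**Step 2: expected events in 82 patients.**

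| SSI rate | Expected SSIs |
|---|---|
| Planning average, 49.5% | 82 × 0.495 = 40.6 |
| Anticipated, 7% | 82 × 0.07 = 5.7 |
| Anticipated, 2% | 82 × 0.02 = 1.6 |

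The planning rates imply about 7 to 25 times as many events as the anticipated rates. The 95% binomial range is 0–4 events at 2% and 2–11 at 7%.

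**Step 3: power with 41 per arm.** All pairs of binomial outcomes were enumerated and each tested at two-sided 5%. Section 2.10.1 gives no rate by arm, so the last three contrasts are assumptions inside its range: two keep the plan's risk ratio of 2, and one takes the two ends of the range.

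| Staples vs Prolene | Chi-square, uncorrected | Fisher |
|---|---|---|
| 66% vs 33% | 88% | 83% |
| 7% vs 3.5% | 10.2% | 1.8% |
| 4% vs 2% | 3.9% | 0.3% |
| 7% vs 2% | 16.6% | 3.1% |

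The normal approximation gives 10.5%, 7.6% and 19% for the last three rows, which leads to the same conclusion. As a plain check, a 5–0 split between arms of 41 gives Fisher p = 0.055; a 6–0 split is needed to reach 0.05.

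**Step 4: precision with 41 per arm.** The 95% half-width for the risk difference, with both arms at rate p, is 1.96 × √(2p(1 − p)/41):

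- p = 2%: 6.1 points
- p = 7%: 11.0 points

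**Step 5: scale.** Sample size for 80% power, two-sided 5%, Fleiss without continuity correction, before any allowance for non-response:

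| Contrast | Per arm |
|---|---|
| 7% vs 3.5% | 637 |
| 4% vs 2% | 1,141 |
| 7% vs 2% | 269 |

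**The case against.** **Nothing is miscalculated.** This is correct. At 66% vs 33% the 82 patients do give at least 80% power (normal approximation: 82% with 37 per arm, 86% with 41). The fault is in the inputs, and the statement about power is conditional on the rates.

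**Difference-test power is the wrong yardstick for an equivalence trial.** Section 2.1 does declare equivalence, and interval width is the more useful quantity for that aim. But Section 2.8 itself powers for a difference, with a risk ratio of 2, so its 80% has to be judged as that claim. Equivalence does not rescue the number either, because an interval of ±6 to ±11 points is wider than the anticipated rates themselves.

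**The 2%–7% may be per knee.** Section 2.10.1 does not say. Counting 164 knees gives about 3 to 11 expected infected knees (164 × 0.02 = 3.3; 164 × 0.07 = 11.5), which does not restore the power. Randomisation and sample size are by patient.

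**Non-response is ignored in the figures for 41 per arm.** True, and allowing for it makes matters worse. With 37 per arm, exact chi-square power over the same three contrasts is about 3–14%, and the half-width is about 6.4–11.6 points.

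**The rates come from sources not seen here.** Section 2.8 cites a study for its inputs, and how 66% and 33% arose cannot be judged from the article. That does not remove the conflict with Section 2.10.1.

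**Re-scoping is a design decision.** This stands. Presenting the trial as estimation or a pilot is one option for the sponsor, and enlarging it is another.

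**Conclusion.** The concern holds and must be fixed. Sections 2.8 and 2.10.1 give incompatible rates for the same primary outcome, and the stated sample size follows from the pair that the protocol does not otherwise expect. At the anticipated 2%–7%, the trial expects about 2 to 6 infected patients. Chi-square power is about 4–17% for the contrasts examined (at most about 3% with Fisher's test), and the 95% half-width is about 6 to 11 points.

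These figures assume the patient as the unit, a two-sided 5% test, 41 evaluable patients per arm and contrasts chosen within the stated range. Counting knees or allowing for non-response does not change the conclusion. It would change only if rates near 66% and 33% were the true expectation, in which case Section 2.10.1 would be wrong.

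**What to change.** 1. In Section 2.8, delete the 66%/33% inputs and the 80% power statement. Recompute from rates that agree with Section 2.10.1, cite their source, and say whether they are per patient or per knee.
2. If 82 patients is the feasible number, state what it delivers: about 2–6 expected SSIs, about 4–17% chi-square power for differences within the anticipated range (about 3–14% with 37 evaluable per arm), and a 95% half-width for the risk difference of about 6–11 points. Give the precision first, since the declared aim is equivalence.
3. Present the SSI comparison as estimation or pilot work, and limit Section 5 so that a non-significant difference is not used to standardise practice.

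**Cost.** With 82 patients kept, this is rewording of Sections 2.8 and 5 with no extra recruitment, but the sponsor has to accept a far less favourable power statement and a narrower claim. If the sponsor prefers to keep 80% power for a doubling, the alternative is a much larger trial: 637 per arm at 7% vs 3.5%, before non-response.

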### 1.3 Hypothesis

#### 1.3.1 Null Hypothesis

There is a difference in the incidence of surgical site infection in bilateral simultaneous TKR patients with wound closure by Prolene vs staple.

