#### 1.3.2 Alternative Hypothesis

There is no difference in the incidence of surgical site infection in bilateral simultaneous TKR patients with wound closure by Prolene vs staple.

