## 2. Methods

### 2.1 Study Design

This study will be conducted as an open blinded, parallel design, equivalence randomized controlled trial. The patients would be randomized to receive either of the two interventions i.e., Prolene or Staples.

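### Section 2.8 sizes the trial to detect a doubling of infection risk, while 1.3 and 2.1 define an equivalence trial, so the stated 80% is not power for the stated hypothesis

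*Protocol article*

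**What the plan says.** Section 2.1 describes the design: "This study will be conducted as an open blinded, parallel design, equivalence randomized controlled trial". The hypotheses match that label. The null in 1.3.1 is "There is a difference in the incidence of surgical site infection in bilateral simultaneous TKR patients with wound closure by Prolene vs staple", and the alternative in 1.3.2 is "There is no difference in the incidence of surgical site infection in bilateral simultaneous TKR patients with wound closure by Prolene vs staple".

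Section 2.8 uses 5% significance, 80% power, 66% surgical site infection with staples and 33% with Prolene, and adds: "The estimated risk ratio taken from a study was 2". After a 10% allowance for non-response it arrives at 82 patients, 41 per arm. Section 2.10.1 anticipates infection rates of 2% to 7%.

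**The concern.** An equivalence trial is sized on a margin, with the true difference taken as zero or close to it. Power is then the probability that the confidence interval falls inside the margin. Section 2.8 instead assumes a true difference of 33 points, a state that belongs to the null hypothesis in 1.3.1. The 80% therefore belongs to the opposite conclusion from the one the trial sets out to support.

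This matters for how the result will be read. With few infections expected, a non-significant difference is likely whatever the truth. A reader could take it as equivalence supported by an 80% power statement. Section 5 plans to circulate the results to the surgeons of the service line so that practice is standardised.

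**Working it through.** **1. Reproducing the plan's figure.** Inputs from 2.8: p1 = 0.66, p2 = 0.33, two-sided α = 0.05 (the sides are not stated; two is my reading), power 0.80. Allocation is 1:1 (2.4).

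n per arm = (1.960 + 0.842)² × 2 × p̄(1 − p̄) / d², with p̄ = 0.495 and d = 0.33. This gives 36.03, rounded up to 37. Then 37 × 1.10 = 40.7, so 41 per arm and 82 in total, an exact match.

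Other forms do not match. The Fleiss form gives 35 per arm (39 after inflation, 78 in total), and with continuity correction 41 (46 after inflation). The one-sided Fleiss form gives 28.

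**2. What the 80% refers to.** Power to detect 66% versus 33% is 82% with 37 per arm and 86% with 41. If those rates were true, the chance of concluding equivalence with 41 per arm (two one-sided 5% tests, normal approximation) would be about 0% for margins of ±10 or ±15 points, 0.2% for ±20 and 5% for ±33. The last is simply the type I error rate, because the truth then sits on the margin.

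**3. Power for equivalence at the anticipated rates.** The article gives no margin, so the margins below are assumptions. Both arms have the same true rate p, from 2.10.1. I use 37 per arm (evaluable) and 41 (randomised), because 41 already contains the non-response allowance. Expected infections per arm at n = 41 are 0.8, 1.8 and 2.9 for p = 2%, 4.5% and 7%. That is too few for a normal-approximation power formula, so I enumerated the binomial tables.

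Power = Σ Bin(x; n, p) × Bin(y; n, p), over all tables (x, y) whose two-sided 90% interval for the risk difference lies inside ±Δ. The Wald interval is d ± 1.645 × √[p̂₁(1 − p̂₁)/n + p̂₂(1 − p̂₂)/n]. The Newcombe interval combines the two Wilson limits.

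| Rate | Margin | Wald, n = 37 / 41 | Newcombe, n = 37 / 41 |
|---|---|---|---|
| 2% | ±5 | 22% / 19% | 0 / 0 |
| 4.5% | ±5 | 3% / 2% | 0 / 0 |
| 7% | ±5 | under 1% / under 1% | 0 / 0 |
| 2% | ±10 | 71% / 78% | 35% / 35% |
| 4.5% | ±10 | 32% / 46% | 13% / 18% |
| 7% | ±10 | 13% / 23% | 4% / 8% |
| 7% | ±15 | 61% / 69% | 49% / 58% |
| 7% | ±20 | 90% / 92% | 84% / 87% |

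The Wald entries at ±5 points come entirely from tables with no infection in either arm, where the interval has zero width. At 2% and 37 per arm that probability is 0.98^74 = 0.224. Without those tables the power is 0.

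The 7% rate is the demanding end. The smallest margin reaching 80% there is 17.6 points (Wald) or 19.6 (Newcombe) with 37 per arm, and 16.8 or 17.8 with 41. So roughly ±20 points covers the whole 2% to 7% range. That is 20/7 = 2.9 times the rate at 7% and 20/2 = 10 times at 2%.

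**4. If the trial were a difference trial.** For a risk ratio of 2 at the anticipated rates, 3.5% versus 7%, the normal-approximation power is 9.9% with 37 per arm and 10.5% with 41. The test would need 637 per arm for 80%.

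**The case against.** *The 33 points could be the equivalence margin.* Two one-sided tests with ±33 points and equal true rates of 33% or 49.5% need 35 or 40 per arm, close to the plan's size. But 2.8 presents 66% and 33% as infection percentages in the two groups and 2 as an estimated risk ratio. A 33-point margin would also accept a doubling from 33% to 66% as equivalent. This reading does not fit the text.

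*A margin may stand in the full protocol or the analysis plan.* It may. The article is a condensed account, and I do not count the absent margin as a fault. The point rests on what 2.8 does state. A margin elsewhere would not turn 66% versus 33% into an assumption of equal rates.

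*The sum is right.* That stands. A reader might infer an arithmetic error, but 82 follows exactly from the stated inputs. The fault is a mismatch between design and sample size.

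*This is the conflict between 66%/33% and the 2% to 7% in 2.10.1 under another name.* It is related but distinct. Putting 2% to 7% into the same formula would still size the trial to find a difference. The power figures at 2% to 7% do draw on that section, so their consequence should not be counted twice.

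**Conclusion.** The point holds: the power statement in 2.8 is wrong as written for the hypothesis in 1.3, and nothing else in the article repairs it. The 80% is the probability of finding a difference when risk doubles.

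The size of the shortfall depends on the assumed margins, equal true rates of 2% to 7%, 37 to 41 evaluable per arm and the interval method. On those terms power is at most about 22% at ±5 points, and 80% across the range needs roughly ±20 points.

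Two stronger readings are tempting and are not supported:

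- One is that power is zero for every margin below the infection rate. Exact zeros partly reflect the normal approximation, and the statement fails at the plan's 33%: with 41 per arm that approximation gives 22% at ±20 points.
- The other is that 41 per arm supports margins as tight as ±9 points at 80%, as the normal approximation suggests for a 2% rate. Enumeration gives only 78% (Wald) or 35% (Newcombe) even at ±10.

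**What to change.** In 2.8, withdraw the statement that 82 patients give 80% power for the stated hypothesis. Then choose one of two routes.

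(a) Keep the equivalence design. State a margin justified on clinical grounds, not worked back from the available number. Report the power that 82 patients (about 74 evaluable) give for it at 2% to 7%, using an exact or score-based method because events are sparse.

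(b) Restate 1.3 and 2.1 as a difference or estimation trial, give power at the anticipated rates (about 10% for 3.5% versus 7%), and state that a non-significant difference will not be reported as equivalence.

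Either route changes only text, but it replaces the 80% with a much less favourable figure. If the sponsor under (a) wanted 80% power at a narrow margin, the cost would be far larger than wording. As an order of magnitude by the normal approximation (one-sided 5% tests), an assumed ±5 points needs 135 per arm at 2% and 447 at 7% before dropout, against one surgeon and one year of recruitment (2.2, 2.9).

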### 2.9 Recruitment

For this study, the non-probability consecutive sampling technique will be used. All the patients opting for surgeon A to undergo elective bilateral simultaneous TKR during the specified period for recruitment will be included in the study. By using the consecutive sampling technique, the probability to miss out on participants would be relatively small. Firstly, the patients opting to undergo bilateral simultaneous TKR under care of the selected surgeon would be identified and would be assessed against the eligibility criteria of the study. Secondly, the eligible patients would be briefed about the study and the interventions of the study. Furthermore, an informed consent would be obtained from the patient. The duration of the trial would be 2 years. During the first year of the study, the participants would be recruited until the desired sample size is achieved. After the surgical procedure, the patients will be followed for a year to assess the incidence of the surgical site infection.

### 2.10 Outcomes

#### 2.10.1 Primary Outcome

Primary outcome of the study is the incidence of surgical site infection (superficial or deep) within 6 weeks for superficial infections and 90 days for deep infections. SSI is defined as an infection that occurs after surgery in the part of the body where the surgery took place within 90 days of surgery [13]. Based on the literature, we anticipate infection rate in the range of 2%–7% [14,15].

#### 2.10.2 Secondary Outcome

The secondary outcomes of the study include the incidence of post-operative complication that includes seroma, hematoma, pain, bleeding within 2 weeks of the surgery. Another outcome of the study would be to assess and compare the pain scores at the time of suture removal.

### 2.11 Outcome Assessment

The outcome will be assessed by the surgical site infection nurse. They will assess the incidence of infection by clinical examination of the wound and pre-validated tools that they are already using during the post-operative follow ups. The secondary outcomes will be assessed by the surgery team through clinical examination. The secondary outcome of pain would be assessed by using the verbal pain score assessment. A case report form (CRF) would be maintained for everyone participating in the study. All the information regarding the individuals i.e., baseline characteristics, lab reports, scans, forms filled by SSI nurses would be maintained in CRF.

## 3. Plan of Analysis

### 3.1 Descriptive statistics

STATA version 15.0 will be used for the statistical analysis. Initially the descriptive statistics will be calculated. For the quantitative variables, the normality assumption would be checked using the Shapiro Wilk test. The mean and standard deviation will be calculated and reported. Median and interquartile range will be reported if the normality assumption for that variable is violated. The qualitative variables will be expressed as the frequencies and proportions.

### 3.2 Univariate and Multivariable Analysis

The Cox Proportional Hazard regression will be used for the univariate and multivariable analysis. Univariate analysis will be conducted, and crude risk ratios and their 95% confidence intervals will be obtained. All significant independent variables at the univariate stage will be regressed by using cox proportional hazard regression using the stepwise method in the multivariable model and the adjusted risk ratios will be obtained. Both per-protocol analysis and intention to treat analysis (ITT) would be performed.

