**Analysis::**

The normality assessment will be done using Shapiro Wilk test. Cox proportional hazard regression will be used to check the univariate and multi-variable associations of independent variables with the outcome. Both intention to treat analysis and per protocol analysis would be performed.

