### 1.2 Objectives

#### 1.2.1 Primary objective

➢ The primary objective of the study is to compare the incidence of surgical site infections (superficial and deep) for Prolene vs staple sutures in the bilateral simultaneous knee arthroplasty patients within 6 weeks for superficial and within 90 days for deep infection.

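### Section 3.2 makes Cox regression the only between-arm method and calls its output risk ratios, although the primary outcome is fixed-window incidence and, at the anticipated rates, an arm may well have no infection

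*Protocol article*

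**What the plan says.** **Method.** Section 3.2 states: "The Cox Proportional Hazard regression will be used for the univariate and multivariable analysis". The Analysis paragraph of the abstract says the same: "Cox proportional hazard regression will be used to check the univariate and multi-variable associations of independent variables with the outcome". No other method for comparing the arms is named. Section 3.1 is descriptive, and its Shapiro–Wilk test serves only to choose between mean and median.

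**Effect measure.** Section 3.2 continues: "Univariate analysis will be conducted, and crude risk ratios and their 95% confidence intervals will be obtained". The multivariable step is described as "using the stepwise method in the multivariable model and the adjusted risk ratios will be obtained". The term hazard ratio does not occur in the article.

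**Question.** The primary objective (1.2.1) is to "compare the incidence of surgical site infections (superficial and deep) for Prolene vs staple sutures". The primary outcome (2.10.1) is the "incidence of surgical site infection (superficial or deep) within 6 weeks for superficial infections and 90 days for deep infections".

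**Rates.** Section 2.10.1 states "we anticipate infection rate in the range of 2%–7" per cent. The sample size (2.8) uses 66% with staples, 33% with Prolene and a risk ratio of 2, and arrives at 82 patients, 41 per arm.

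**The concern.** The objective, the outcome definition and the sample size all concern the proportion of patients infected within a set time. Section 3.2 fixes a model that estimates a ratio of hazards and gives its output the name of a different quantity. A reader of the results could not tell whether a reported risk ratio was a ratio of fixed-window risks or a hazard ratio.

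The more practical difficulty is sparse events. If one arm has no infection, the Cox partial likelihood is monotone, the estimated hazard ratio runs to zero or infinity, and the usual Wald interval is useless. If neither arm has an infection, there is nothing to estimate. What is at stake is a primary analysis that may return no finite estimate although the two observed proportions can always be compared.

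**Working it through.** **Inputs.** 41 patients per arm and the 66%, 33% and risk ratio of 2 come from 2.8. The 2% to 7% range comes from 2.10.1. Allocation is 1:1 by patient (2.4). Assumptions: 2% to 7% is a per-patient risk, the true rate is the same in both arms unless stated, and the 5% level is two-sided (2.8 does not say).

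**1. The plan's own figure.** With average rate (0.66 + 0.33)/2 = 0.495, the Kelsey formula gives

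n = (1.96 + 0.8416)² × 2 × 0.495 × 0.505 / 0.33² = 36.03, so 37 per arm.

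Then 37 × 1.10 = 40.7, so 41 per arm and 82 in total. The stated size is reproduced, but only from the 66% and 33% rates.

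**2. Expected infections.** At the planning rates: 41 × (0.33 + 0.66) = 40.6. At the anticipated rates: 82 × 0.02 = 1.6, 82 × 0.045 = 3.7 and 82 × 0.07 = 5.7.

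**3. Chance of an arm with no infection.** For one arm it is (1 − p)^41. For at least one of two arms it is 1 − [1 − (1 − p)^41]².

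| Rate in both arms | One given arm empty | At least one arm empty | Both arms empty |
|---|---|---|---|
| 2% | 0.437 | 68% | 19% |
| 3% | 0.287 | 49% | 8% |
| 4.5% | 0.151 | 28% | 2% |
| 7% | 0.051 | 10% | 0.3% |

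With a true risk ratio of 2 inside the range, the chance of at least one empty arm is 54% (2% against 4%) and 27% (3.5% against 7%). With 37 evaluable patients per arm it is 72% at 2%, 33% at 4.5% and 13% at 7%. At 33% against 66% it is effectively nil.

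**4. Sensitivity to the unit.** Section 2.10.1 does not say whether its rate is per patient or per knee. If it is per knee and the two knees are independent (an assumption), the exponent becomes 82. The chance of at least one empty arm is then about 35% at 2% and 0.5% at 7%.

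**5. Size of the mislabelling.** Under proportional hazards the hazard ratio implied by two risks is ln(1 − p₁)/ln(1 − p₂).
- 66% against 33%: ln(0.34)/ln(0.67) = 2.69, for a risk ratio of 2.
- 7% against 3.5%: ln(0.93)/ln(0.965) = 2.04, for a risk ratio of 2.

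**6. What a fixed-window comparison gives.** With 2/41 in each arm, each proportion is 4.88% with Wilson limits 1.35% and 16.14%. The Newcombe limits for the difference are ±√(3.53² + 11.26²) = ±11.8 percentage points. For 0/41 against 2/41 the interval is −16.1 to +4.4 points, and for 0/41 against 0/41 it is ±8.6 points. It is finite in every case, though wide. The risk ratio at 2 against 2 has the log-method interval exp(±1.96 × √(2/2 − 2/41)) = 0.15 to 6.8. With an empty arm it too is zero, infinite or undefined.

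**The case against.** The strongest reply has five parts.

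- **The two harms do not occur together.** Where the label changes the number, at 33% and 66%, events are plentiful. Where events are sparse, the label changes almost nothing. This is right, and the two must be argued separately.
- **Sparse events come from the sample size.** They follow from sizing the trial at 33% and 66% while anticipating 2% to 7%, and changing the estimator does not add information. This also stands: ±11.8 points is imprecise against rates of 2% to 7%. But the trial as written has 41 per arm, and at that size the choice of method decides whether a finite estimate is available.
- **An empty arm does not end a Cox analysis.** Score and likelihood-ratio tests, and a profile-likelihood interval bounded on one side, remain available when one arm has events, and 3.2 does not commit to Wald intervals. This stands, but 3.2 does not say what would be done.
- **The label may be intended.** Cox regression with a constant follow-up time is sometimes used to obtain risk ratios. Nothing in the article says that this is meant.
- **A risk difference is partly a preference.** No equivalence margin or scale is stated, the only effect measure in 2.8 is a risk ratio, and Cox handles censoring where crude proportions do not. This stands as to scale and censoring. It does not remove the mismatch between a hazard-based model and a fixed-window outcome.

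A reader might also infer that Cox regression is prescribed for the pain scores at suture removal and for the 2-week complications. The article does not say so. The abstract speaks of a single outcome, and methods for secondary outcomes may stand in an analysis plan that is not shown. No point is made of them here.

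**Conclusion.** The point holds in a limited form and should be corrected. The only between-arm method named yields hazard ratios, its output is called risk ratios, and it does not directly estimate incidence within the stated windows. At the article's own anticipated rates there is a material chance of no finite Cox estimate: about 68% at 2%, 28% at 4.5% and 10% at 7%. These figures rest on 41 patients per arm, a per-patient reading of the rate and equal rates in the two arms.

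A reader might go further and say that the primary estimate will usually be infinite. That is not supported. On the equal-rate per-patient reading the chance reaches about one half or more only at 3% and below. It falls sharply on a per-knee reading and is negligible at the planning rates, and the result may equally be zero or undefined. Nor do the documents support saying that the label will seriously distort the result at low rates, where 2.04 replaces 2.

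**What to change.** Reword 3.2 as follows.

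- **Primary comparison:** the difference between arms in the proportion of patients with SSI within the windows of 2.10.1, with a Newcombe or Miettinen–Nurminen 95% interval.
- **Supplement:** the risk ratio for the same windows, where it can be estimated.
- **If Cox regression is kept:** make it a secondary time-to-infection analysis, call its output crude and adjusted hazard ratios, and state that Firth penalisation or profile-likelihood intervals will be used if one arm has no events. If neither arm has an event, no hazard ratio can be reported, and the plan should say so.

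The Analysis paragraph of the abstract should be brought into line.

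The cost is a few sentences, with no new data. The small downside is that crude proportions do not handle censoring, which the secondary Cox analysis covers. The change does not cure imprecision: the interval is still about ±12 points at two infections per arm. The conflict between the rates in 2.8 and 2.10.1 needs its own resolution.
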